### Sample size

The primary outcome in the NET trial is appropriate PTA screening. In the calculation of sample size for this outcome, adjustment needs to be made for the clustered nature of the design. The variance inflation factor, or design effect, used to achieve this is a function of the average cluster size, variation in cluster size, and the intra-cluster correlation (ICC) [79].

The assumed ICC was calculated from two sources reporting ICCs from various datasets [80,81]. We included only ICCs for process measures in secondary care settings since empirical research has demonstrated that ICCs tend to be larger for 1) process measures compared with patient outcomes (median 0.063 versus 0.030, respectively), and 2) secondary care compared with primary care (median 0.061 versus 0.045) [63]. Thirty three ICC estimates for process measures in secondary care were available, and the median ICC was 0.18. The variation in cluster size was incorporated into the sample size calculation through an estimate of the coefficient of variation, defined as the ratio of the standard deviation of the cluster sizes to the mean cluster size [79]. The estimated coefficient of variation of 0.47 was calculated from annual attendance at EDs across 170 hospitals in Australia in 2009.

There were limited studies providing estimates of rates of compliance for our primary outcome [82], and no studies undertaken in adult populations. We therefore undertook a retrospective audit of two Australian metropolitan EDs. The estimated rates of appropriate PTA screening for patients presenting in these hospitals (with an initial GCS of 14 or 15) were 0% (95% CI 0% to 14%; n = 24) in one hospital, and 31% (95% CI 24% to 39%; n = 164) for a second (which had an mTBI protocol in place) ([name], [name], unpublished observations). We expected that hospitals without a protocol for mTBI would be more interested in participating in the trial, and therefore calculated our sample size based on a control group rate of 10% (that is, closer to the estimated rate in the hospital with no protocol in place). We wish to detect an absolute increase in the rate of appropriate PTA screening of at least 20%. Our rationale for selecting a difference of 20% is based on considering the size of effect required to justify a resource intensive intervention such as NET, and estimates of the effects of local opinion leaders on professional practice observed across a range of studies [83].

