To detect an absolute increase of 20% in the rate of appropriate PTA screening (equivalent to an odds ratio of 3.9, log odds 1.3) (assuming a control group rate of 10%, an ICC of 0.18, coefficient of variation = 0.47, an average of 30 patient participants per ED, and a 5% significance level) with 80% power, we will require 15 EDs per intervention group. A total of 30 EDs will provide 900 patient participants for whom ED staff management will be assessed. For 900 patient participants, the width of the 95% confidence interval for the observed difference in appropriate PTA screening rates between groups will be approximately ±14% (equivalent to a width of ±0.51 on the log odds scale). Allowing for 10% attrition in EDs, we plan to initially recruit 17 EDs per intervention group.

Power is dependent on the selected parameters, but in cluster trials is primarily determined by the chosen ICC and control group rate. Assuming all other parameters are as defined above, a lower control group rate (for example, 5%) will result in greater power (87%), while a higher control group rate (for example, 30%) would result in less power (60%). A smaller ICC (for example, 0.10) would result in greater power (94%), while a larger ICC (for example, 0.30) would result in less power (59%).

Sample size calculations were undertaken using the module *clustersampsi*[84] implemented in the statistical package Stata (StataCorp LP, USA) [85].

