### Effectiveness analysis

The effectiveness of the intervention on management outcomes, predictors of management outcomes, and patient outcomes will be estimated with marginal modelling using generalised estimating equations. These models will appropriately account for correlation of responses of individuals within EDs. We plan to fit an exchangeable correlation structure where responses from the same ED are assumed to be equally correlated [86]. We will use robust variance estimation which yields valid standard errors even if the within-cluster correlation has been incorrectly specified [87,88]. For binary outcomes, a logit link will be used.

Models will include adjustment for minimisation factors (size (annual presentation rate in 2012), existence of an mTBI protocol, NET or NET-Plus, and rurality) and pre-specified potential confounding variables (Figure 3). The potential confounding variables have been selected through discussion amongst the investigators and from published research. All pre-specified confounders will be included in the models even when no baseline imbalance exists. In addition, for continuous outcomes which are collected at both baseline and follow-up (for example, clinicians’ self-reported cognitions, social and environmental influences in relation to the key behaviours, cognitions about their organisation and team climate) we will include the baseline measure of the outcome in the model. Adjustment for the baseline measure of a continuous outcome yields unbiased estimates of intervention effect in circumstances where there is baseline imbalance, and has the benefit of providing the most powerful analysis [89]. Our primary effectiveness analysis will be the model (as described above) that estimates the intervention effect on the primary outcome, appropriate PTA screening.

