**Figure 3 F3:**
[figure not shown]
**Confounders.** mTBI, mild traumatic brain injury; NET, Neurotrauma Evidence Translation.

Estimates of intervention effect from these models with binary outcomes will yield odds ratios. To aid interpretability, we plan to also provide estimates of risk differences [90]. Estimates of risk differences will be computed from marginal probabilities estimated from the fitted logistic models [91].

Missing data for the clinical practice outcomes are likely to be minimal since eligible patients will be identified and data extracted through chart audit. Missing data could arise if EDs choose to withdraw post-randomisation but prior to data being extracted from clinical records, resulting in empty clusters. Accounting for empty clusters requires strong assumptions to be made about patient characteristics and outcomes based on ED staff or ED characteristics. We will attempt to examine the potential impact of empty clusters on the intervention effects for the clinical practice outcomes using weights to allow for patterns of ‘missingness’ [92]. For continuous outcomes, generalised estimating equations yield unbiased estimates of intervention effect when 1) data are missing completely at random, or 2) when the correlation structure is correctly specified and known covariates that are associated with the missing data mechanism are included in the model (missing at random) [93,94]. For the continuous proxy measures of clinical practice and hypothesised mediators, we plan to identify potential predictors of missing data through modelling (for example, [95]), and include these predictors in the primary analysis model. We will investigate methods to impute missing outcome data collected at baseline (for example, baseline behavioural constructs) [96].

All estimates of intervention effect will be reported with 95% confidence intervals. No adjustment will be made for multiple testing. All tests will be two-sided and carried out at the 5% level of significance. A full statistical analysis plan will be developed and written prior to undertaking any data analysis.

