Potential confounders at patient level are collected via chart audit. Potential confounders at the level of staff members, as well as organisational history of change [97], organisational learning [98], leadership [99], staff culture [99] and team tenure [100] will be collected via self-report surveys. ED structural characteristics will be measured via a telephone checklist completed by the ED Director (or delegate).

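### Forcing every pre-specified confounder into the primary model may put about 9–10 ED-level terms on 30–34 EDs, which the unadjusted power calculation does not allow for

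*Protocol article*

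**What the plan says.** Effectiveness analysis specifies generalised estimating equations (GEE) with a logit link for binary outcomes, an exchangeable correlation and robust variance estimation. It describes the robust standard errors as valid even when the working correlation is wrong. The models adjust for four minimisation factors, all properties of the ED (size, mTBI protocol, NET or NET-Plus, rurality), and for pre-specified potential confounders. The inclusion rule has no exception: "All pre-specified confounders will be included in the models even when no baseline imbalance exists". The same section then says "Our primary effectiveness analysis will be the model (as described above", applied to appropriate PTA screening.

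The paragraph after Figure 3 gives the sources of the confounders. Patient-level items come from the chart audit. For the organisational constructs, listed in one sentence with the staff-level items, it reads: "organisational history of change [97], organisational learning [98], leadership [99], staff culture [99] and team tenure [100] will be collected via self-report surveys". A checklist completed with the ED Director supplies the structural characteristics of the ED.

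Sample size states "with 80% power, we will require 15 EDs per intervention group", for 10% against 30%, with "an ICC of 0.18, coefficient of variation = 0.47, an average of 30 patient participants per ED, and a 5% significance level". Allowing for 10% ED attrition, 34 EDs are to be recruited. No covariate enters that calculation.

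**The concern.** The primary outcome is audited per patient, and the article describes no link from an audited patient to a surveyed staff member. An organisational survey score can therefore enter the primary model only as one value per ED. Four minimisation factors plus five organisational constructs make nine ED-level terms, and one structural characteristic makes ten.

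The intervention is also an ED-level variable, so it competes with these terms for the information in about 30 clusters. This has two consequences:

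- **Power.** Chance imbalance on several ED-level terms inflates the variance of the intervention effect, and each term uses a cluster-level degree of freedom. Unless the terms explain enough outcome variation to compensate, a true 20-point gain may be missed.
- **Level.** The validity of the robust standard error is a property of many clusters. With 30 clusters and ten or so cluster-level terms it is too small, and false positives exceed 5%.

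**Working it through.** **Inputs (Sample size, Effectiveness analysis).** Control rate 10%; difference 20 points (10% v 30%); intra-cluster correlation (ICC) 0.18; coefficient of variation (CV) of cluster size 0.47; mean 30 patients per ED; two-sided 5%; 80% power; 15 EDs per arm; 34 EDs recruited; four minimisation factors; five named organisational constructs. The number of structural characteristics beyond the minimisation factors is not given; I assume 0 or 1, with one term per variable.

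**1. Reproduce the plan's figure.**
- Design effect = 1 + [(CV² + 1)m − 1] × ICC = 1 + [(0.2209 + 1) × 30 − 1] × 0.18 = 7.413.
- Patients per arm before inflation = (1.960 + 0.842)² × (0.10 × 0.90 + 0.30 × 0.70) / 0.20² = 58.87.
- EDs per arm = 58.87 × 7.413 / 30 = 14.55, so 15. This agrees with the plan.
- With 15 per arm, SE = √(0.30 × 7.413 / 450) = 0.0703 and 0.20 / 0.0703 = 2.845. Power is 0.81 (normal) or 0.78 (t, 28 df). The t version also matches the plan's sensitivity figures: 0.873, 0.602, 0.938 and 0.590 against 87%, 60%, 94% and 59%.

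The calculation is sound for an unadjusted comparison.

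**2. Analytic cost of the extra ED-level terms.** For terms unrelated to outcome, the expected variance inflation from chance imbalance on q of them is (d − 3)/(d − q − 3). Here d is the number of EDs less the terms already balanced. Residual df are 30 − 2 − (all covariate terms).

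| Case | Variance factor | df | Power |
|---|---|---|---|
| Four balanced factors + 5 terms | 23/18 = 1.28 | 19 | 0.67 |
| Four balanced factors + 6 terms | 23/17 = 1.35 | 18 | 0.64 |
| Chance imbalance on all 9 | 27/18 = 1.50 | 19 | 0.60 |
| Chance imbalance on all 10 | 27/17 = 1.59 | 18 | 0.57 |
| All terms perfectly balanced | 1.00 | 19 or 18 | 0.77 |

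Each power uses the noncentral t with noncentrality 2.845/√factor.

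**3. Simulation of the planned GEE.** Logit link, exchangeable correlation, beta-binomial or logit-normal outcomes, three binary factors balanced by arm plus size, 3,200 to 4,000 runs per cell, null rate 10% or 20%.

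True level of the uncorrected robust Wald z test at nominal 5%, 30 EDs:

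| ED-level covariates | True level |
|---|---|
| None | 0.07–0.10 |
| 4 (minimisation factors) | 0.09–0.15 |
| 9 | 0.16–0.22 |
| 10 | 0.17–0.23 |

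Power at a true 5% level (critical value set from the null runs), 9–10 terms:

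| Between-ED variance explained by the covariates | 30 EDs | 34 EDs |
|---|---|---|
| None | 0.62–0.69 | 0.72–0.79 |
| 20% | 0.70–0.76 | 0.76–0.82 |
| 30% | 0.73–0.80 | 0.79–0.86 |
| 50% | 0.80–0.86 | 0.88–0.91 |

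With all 34 EDs the uncorrected level is still 0.13–0.21. With 30 EDs, a Kauermann–Carroll standard error and a t reference give a level of about 0.06–0.08 and power of 0.69–0.72 for non-prognostic terms. A separate simulation of a valid ED-level regression gave power of 0.81 with four terms and 0.70 with ten.

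**4. Break-even for six added terms.** The variance factor 23/17 = 1.353, times the squared ratio of t critical values (2.101/2.064)² = 1.036, gives 1.40. The six terms must jointly explain 1 − 1/1.40 = 0.29 of the residual ED-level variance before they pay for themselves.

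**The case against.** The confounder list is in Figure 3, which cannot be seen here. Effectiveness analysis covers management outcomes, predictors and patient outcomes together, and the confounder paragraph lists sources for all of them. Staff-level confounders have no obvious place in a chart-audit model, so Figure 3 may well assign confounders by outcome. If it keeps the organisational constructs and structural items out of the PTA model, the point about added terms falls. This stands, so the point is conditional.

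A reader might infer that the trial cannot reach 80% power. The documents do not support that. The confounders were chosen partly from published research, so purely non-prognostic terms are the unfavourable end of the range. The two-ED audit (0%, and 31% where a protocol existed) suggests that the protocol factor could be strongly prognostic, and the power calculation takes no credit for it.

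A reader might also quote far lower power from a Mancl–DeRouen correction with t (0.39–0.69). That test runs at 0.01–0.02 here, so much of the loss is conservatism and not power at a true 5% level.

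Adjusting for pre-specified covariates regardless of imbalance is accepted practice, and a small-sample correction is commonly left to the statistical analysis plan, so its absence alone is no finding. What remains is that the article itself fixes the inclusion rule and the primary model, and sizes the trial for a different, unadjusted analysis.

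**Conclusion.** The point holds conditionally. If the named organisational and structural confounders enter the primary model, as the inclusion rule reads, the stated sample size does not support 80% power at a true 5% level for that model unless the covariates are substantially prognostic. With 30 EDs the uncorrected robust test has a false-positive rate three to four times nominal or more, although part of that excess is already present with the minimisation factors alone. Once the level is corrected, the trial falls 10 to 18 points short of 80% if the added terms are not prognostic.

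The size rests on these assumptions: one term per ED-level variable, at most one structural item beyond the minimisation factors, patient-level confounders left out of the simulation, and minimisation approximated by balancing three binary factors. The documents do not say how prognostic the organisational scores are.

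**What to change.** In the analysis plan, before any analysis:

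- Limit the ED-level terms in the primary model to the four minimisation factors. Patient-level covariates can stay, since they cost no ED-level degrees of freedom.
- Move the organisational scores and other ED structural characteristics to a pre-specified sensitivity analysis, and state that the primary conclusion rests on the reduced model.
- Name a small-sample-corrected robust standard error with a t reference for the primary test. Cutting terms does not restore the level by itself: with the four factors it is still 9–15%.
- If Figure 3 already keeps these constructs out of the PTA model, say so in the text of Effectiveness analysis.

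The cost is wording only; the article reports that data cleaning and analysis had not begun. The downside is some lost precision if the organisational scores explain more than about 29% of residual ED-level variance.

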**Figure 3 F3:**
[figure not shown]
**Confounders.** mTBI, mild traumatic brain injury; NET, Neurotrauma Evidence Translation.

Estimates of intervention effect from these models with binary outcomes will yield odds ratios. To aid interpretability, we plan to also provide estimates of risk differences [90]. Estimates of risk differences will be computed from marginal probabilities estimated from the fitted logistic models [91].

Missing data for the clinical practice outcomes are likely to be minimal since eligible patients will be identified and data extracted through chart audit. Missing data could arise if EDs choose to withdraw post-randomisation but prior to data being extracted from clinical records, resulting in empty clusters. Accounting for empty clusters requires strong assumptions to be made about patient characteristics and outcomes based on ED staff or ED characteristics. We will attempt to examine the potential impact of empty clusters on the intervention effects for the clinical practice outcomes using weights to allow for patterns of ‘missingness’ [92]. For continuous outcomes, generalised estimating equations yield unbiased estimates of intervention effect when 1) data are missing completely at random, or 2) when the correlation structure is correctly specified and known covariates that are associated with the missing data mechanism are included in the model (missing at random) [93,94]. For the continuous proxy measures of clinical practice and hypothesised mediators, we plan to identify potential predictors of missing data through modelling (for example, [95]), and include these predictors in the primary analysis model. We will investigate methods to impute missing outcome data collected at baseline (for example, baseline behavioural constructs) [96].

All estimates of intervention effect will be reported with 95% confidence intervals. No adjustment will be made for multiple testing. All tests will be two-sided and carried out at the 5% level of significance. A full statistical analysis plan will be developed and written prior to undertaking any data analysis.

Potential confounders at patient level are collected via chart audit. Potential confounders at the level of staff members, as well as organisational history of change [97], organisational learning [98], leadership [99], staff culture [99] and team tenure [100] will be collected via self-report surveys. ED structural characteristics will be measured via a telephone checklist completed by the ED Director (or delegate).

### Process evaluation

Our theory-based evaluation of factors along the proposed causal pathway (see Table 4 and Figure 2) will be complemented by other components that form part of our process evaluation [101,102]; these are: 1) an assessment of intervention fidelity (whether the intervention was successfully and consistently delivered as planned (delivery), and whether it reached the target group (receipt)) [103,104]; 2) perceptions of success of delivery and receipt [105], and factors that contributed to this [103]; and 3) perceptions of acceptability and feasibility of the roll-out of the intervention [106].

Table 6 summarises the main elements included in the evaluation, methods planned, and indicative measures. A more detailed description of the fidelity assessment will be provided in a future publication.

**Table 6 T6:** Overview of mixed-methods process evaluation

**Element**	**Method**	**Indicative measures/details**
Theory-based evaluation of factors along the proposed causal pathway	Quantitative	**Intervention and control group**: scales in endpoint surveys (see Table 4)
Delivery of intervention components	Mixed	**Intervention group**: detailed assessment of NET intervention delivery
		Local opinion leaders: researcher-assessed presence of both opinion leaders in each hospital for entire intervention delivery duration
		Stakeholder meeting: attendance of providers; delivery of messages and so forth (researcher assessed)
		Train-the-trainer: observer assessment of intervention components
		Local educational workshops: education sessions provided assessed via log-books completed by the clinical opinion leaders
		Materials and tools: availability assessed via self-report clinical opinion leaders and staff
		**Control group**: high-level assessment of potential delivery of (non-NET) intervention components assessed via a brief telephone interview with ED Director or delegate (for example, was someone in your ED championing improvements/providing education around the management of mTBI patients?)
Receipt and acceptability and feasibility of intervention elements	Mixed	**Intervention group**:
		Local opinion leaders: inclusion ‘local opinion leaders’ scale (ORCA) in staff endpoint surveys; staff perceptions of ‘availability’ and ‘credibility’ (in semi-structured interviews)
		Stakeholder meeting: attendance of key-stakeholders; acceptance of messages (both researcher assessed)
		Train-the-trainer: attendance of local opinion leaders assessed via attendance lists; participant assessment of acceptance of components (participant sheets)
		Local educational workshops: attendance of local staff assessed via attendance lists; participant acceptance of sessions provided, assessed via scales in endpoint surveys and semi-structured evaluation interviews
		Materials and tools: availability assessed via self-report of local opinion leaders and staff
Perceptions around successful implementation	Qualitative	**Intervention group**: Perceptions around the success of the implementation assessed in semi-structured interviews
Perceptions of factors influencing successful implementation	Mixed	**Intervention group**: Perceptions around factors influencing the implementation processes (for example, organisational readiness; perceived leadership support; perceptions around quality and clarity of evidence and recommendations and so forth, measured in semi-structured interviews)
		Inclusion of ‘leadership’ scale (ORCA) in staff endpoint surveys
Perceptions of acceptability and feasibility intervention as ‘package’	Mixed	**Intervention group**: Perceptions around usefulness and feasibility of roll-out measured in semi-structured interviews

ED, emergency department; mTBI, mild traumatic brain injury; NET, Neurotrauma Evidence Translation; ORCA, organisational readiness to change assessment.

We plan to conduct semi-structured interviews with ED Directors, local opinion leaders and staff members in eight intervention hospitals. We will sample for maximum variation (for example, size and location of EDs). The interview guide and analyses will be guided by a theory-based framework that was used in phase two of this project (the interview phase). Analyses and interviewing will be done concurrently to inform emerging themes. If data saturation has not been reached after conducting interviews in eight hospitals, we will add sites and continue sampling until data saturation [107].

In addition, a brief checklist-guided structured interview will be conducted by telephone with ED Directors or delegates to assess sustainability of the changes in intervention hospitals (for example, plans to integrate a validated tool into charts).

